#### Suicidal behaviour (secondary outcome)

Suicidal behaviour will be measured using 2-items from the 4-item version of the Suicidal Behaviour Questionnaire-Revised (SBQ-R) [21]. The first item assesses the frequency of suicidal ideation in the past 6 months, and responses will be dichotomised (never/ever). The second item measures the likelihood of suicidal behaviour in the future (no chance/unlikely/likely).

#### Psychological distress (secondary outcome)

Psychological distress will be measured using the Kessler-6 instrument (K6) [22]. Participants will be asked to indicate the response that best describes their feelings in the past 4 weeks. Responses will be made on a 5-point Likert scale ranging from 0 (*none of the time*) to 4 (*all of the time*). The six items will be summed to give a score ranging from 0 to 24.

#### Health service use (economic evaluation)

Health service use will be assessed using a modified version of the self-report measure of the Resource Use Questionnaire [23] developed for use in this study. Five questions will assess participants’ use of a range of health services for mental health difficulties over the preceding 6 months, including primary health services (e.g. consultations with a general practitioner, psychologist) and inpatient admissions (e.g. hospital, community care unit). Use of psychotropic medications (e.g. sleeping tablets, antidepressants) is also assessed, as is the effect of mental health difficulties on functioning at work and absence from work.

#### Covariates

Name & mobile telephone contact number (for within-person linking of baseline and final assessments), company/site name (for cluster identification), age, gender, occupation, Aboriginal and Torres Strait Islander status, Australian-born versus born outside Australia, history of previous training in MATES programs (Construction, Energy, or Mining).

### Measures (2): implementation evaluation

We will monitor and record the number of program activities and participation levels in program activities (e.g., percent of workers on site attending GAT; number and percent of GAT trainees recruited and successfully trained as Connectors). In addition, we will measure suicide prevention literacy as a process/implementation measure using the literacy of suicide scale short form (LOSS). Each of the items on the LOSS is responded to on a 3-point scale (“True”, “False”, or “I don’t know”), with correct responses allocated a score of 1 and incorrect or “I don’t know” responses assigned a score of 0 (e.g., sample item: “People who have thoughts about suicide should not tell others about it”). Total scale scores are calculated by summing item scores, yielding a total literacy score (per cent correct). The LOSS has been validated by using Item Response Theory to identify items that had the strongest discrimination of the underlying literacy construct [24].

### Analysis (1): quantitative effectiveness evaluation

The primary analysis will be undertaken on an intention-to-treat basis: including all participants as randomised, regardless of treatment received or withdrawal from the study. Mixed-model Repeated Measures (MMRM) analyses will be used because of the ability of this approach to include participants with missing data. Cluster effects will be modelled using a random site effect. An unstructured residual variance-covariance matrix will accommodate within-participant dependency. The statistical significance of the primary outcome will be evaluated in a planned comparison of change from baseline to 8 months post-initiation of intervention in the active arm compared to 8-month change in the waitlist group. Tests of significance will use appropriate degrees of freedom adjustment where necessary (i.e., the Kenward-Roger method based on the observed information matrix). Where necessary, transformation of the outcome variable will be undertaken to ensure distributional assumptions of the model are met.

For binary outcomes (prevalence of suicidal ideation) and other non-continuous outcomes (severity of suicidal thoughts and behaviours), comparable generalized mixed models will be used with population average effects of intervention being compared.

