### Sequence generation, randomisation and allocation concealment

Allocation of sites (clusters) to intervention arms will be conducted by the project statistician (AM) using minimisation implemented with the *rct_minim* procedure in Stata. Balance will be sought for a single factor – site size – with sites of less than 150 workers classified as ‘small’ and sites of 150 or more workers classed as ‘large.’ Due to resource limitations, participating sites will be randomly assigned to intervention or wait-list control in small batches of up to four sites (further detail below). Allocations will then be revealed to the research team, MATES field staff and sites, as blinding beyond the baseline assessments will not be feasible.

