#### Power and sample size

We based our power and sample size calculations on the primary outcomes: intentions to seek help from formal sources. From a previous MATES trial in construction workers (“MATES Mobile,” ACTRN12619000625178) [25], we obtained clustered data with which to estimate intra-class correlation (ICC) and the corresponding design effect. Our measure of intention to seek help for emotional problems from formal sources yielded an ICC estimate of 0.0112. To be conservative, we used an ICC of 0.02. For our anticipated effect size, or Minimally Important Difference (Cohen’s d, standardised difference in change between intervention and control groups in a two-arm trial), we have used 0.30; this effect size is modest, but is in the range of what has been achieved in previous workplace suicide prevention trials. Other inputs into power calculations included: alpha = 0.05 and beta = 0.80. Because we did not know in advance what our cluster sizes would be, a set of calculations was conducted assuming a range of anticipated cluster sizes (30, 50 and 100 workers per cluster/site). At the lower cluster size of 30, we would need 19 sites, at the middle cluster size of 50 we would need 14 sites, and finally if our cluster sizes average 100 or more, we would need only 10 sites. Hence the target sample size in this protocol is estimated at 1000, based on recruiting 10 sites of 100 workers each, acknowledging that the final sample size may vary based on worksite size.

In addition, we will conduct exploratory analyses to investigate whether intervention-associated changes differ by gender or by manual blue-collar versus white-collar.

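### As worded, the primary model has no term for site-to-site variation in change, so the arm-by-time test may understate its standard error by an amount the protocol does not allow one to fix

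*Protocol article*

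**What the plan says.** Sites are the unit of allocation: "Allocation of sites (clusters) to intervention arms will be conducted by the project statistician" (Sequence generation, randomisation and allocation concealment). Workers are surveyed at baseline and at 8 months, and names and phone numbers are collected "for within-person linking of baseline and final assessments" (Covariates).

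The section Analysis (1): quantitative effectiveness evaluation fixes four things for the primary outcome:

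- the cluster term and the within-person term: "Cluster effects will be modelled using a random site effect. An unstructured residual variance-covariance matrix will accommodate within-participant dependency";
- the tested contrast: "planned comparison of change from baseline to 8 months post-initiation of intervention in the active arm compared to 8-month change in the waitlist group";
- the degrees of freedom, where an adjustment is needed: "the Kenward-Roger method based on the observed information matrix".

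No site-by-time term is mentioned. Comparable generalised mixed models are planned for the binary and other non-continuous outcomes.

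Power and sample size defines the target effect (d = 0.30) as a standardised difference in change. It reports an ICC of 0.0112 for the intention measure in an earlier trial and then pads it: "To be conservative, we used an ICC of 0.02". It arrives at 19, 14 or 10 sites for 30, 50 or 100 workers per site.

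**The concern.** In a two-wave cluster trial analysed by change, the between-site variance that matters is the variance of the sites' *changes*. Local management, an incident, COVID-19 disruption or uneven roll-out can move a whole site up or down between the waves. A site intercept common to both waves absorbs stable differences between sites but not these movements. The residual matrix acts within participant, so changes of workers at the same site are treated as independent. Kenward-Roger adjusts only for variance components that are in the model. Without a site-by-time term it yields degrees of freedom on the scale of workers rather than sites.

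If sites do differ in change, the primary p-value is too small and the interval too narrow, and a chance difference among about ten sites could be reported as a program effect. The economic evaluation depends on this same test, and the generalised models for the secondary outcomes would inherit the gap.

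**Working it through.** **1. Reproduce the plan's sample size.** Two-sided alpha 0.05 (two-sided assumed), power 0.80, d = 0.30: 176 per arm with the t-distribution (175 normal), so 352 in total. Multiply by 1 + (m − 1) × 0.02 and divide by m:

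- m = 30: 352 × 1.58 / 30 = 18.5
- m = 50: 352 × 1.98 / 50 = 13.9
- m = 100: 352 × 2.98 / 100 = 10.5

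To the nearest whole number (10.49 before rounding in the last case) these are the stated 19, 14 and 10. The sample size therefore does apply a design effect to the difference in change.

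**2. What the model as worded leaves out.** Let ICC be the site share of variance at one wave, r the correlation of a site's effect between waves, and w the within-person correlation given site. Neither r nor w is in the document; both are assumed. Then:

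- variance of a site's change: 2 × ICC × (1 − r)
- variance of a worker's change within site: 2 × (1 − ICC) × (1 − w)
- ICC of change = ICC(1 − r) / [ICC(1 − r) + (1 − ICC)(1 − w)]
- design effect = 1 + (m − 1) × ICC of change
- actual type I error at nominal 5% = 2[1 − Φ(1.96 / √design effect)]

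The last line uses a normal reference because the model's degrees of freedom are large.

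Example (ICC 0.02, r = 0.9, w = 0.5, m = 100): ICC of change = 0.002 / (0.002 + 0.49) = 0.00407; design effect = 1 + 99 × 0.00407 = 1.40; type I error = 2[1 − Φ(1.655)] = 9.8%.

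**3. Type I error at 100 per site, all workers with both surveys** (w = 0.5 / w = 0.6):

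| r | ICC 0.0112 | ICC 0.02 |
|---|---|---|
| 1.0 | 5.0% / 5.0% | 5.0% / 5.0% |
| 0.9 | 7.6% / 8.3% | 9.8% / 11.0% |
| 0.8 | 10.3% / 11.6% | 14.4% / 16.6% |
| 0.5 | 17.7% / 20.4% | 25.6% / 29.2% |

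Smaller sites give less: with ICC 0.0112, r = 0.9 and w = 0.5, the figures are 5.8% at 30 per site and 6.3% at 50.

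**4. If the ICC of change itself were 0.02.** Design effects of 1.58, 1.98 and 2.98 give 11.9%, 16.4% and 25.6% at 30, 50 and 100 per site. From the formula in step 2, a score ICC of 0.02 implies a change ICC of 0.02 only when r = w, that is, when site effects are no more stable over 8 months than a worker's own answers.

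**5. Simulation of the model as worded** (REML, one site intercept plus an unstructured 2 × 2 residual, 10 sites of 100, ICC 0.02, 600 runs per setting):

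| r | w = 0.5 | w = 0.6 |
|---|---|---|
| 1.0 | 5.2% | 4–5% |
| 0.9 | 7.8% | 11% |
| 0.8 | 15.2% | 17% |
| 0.5 | 26.3% | 31% |

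With 20% baseline-only and 20% follow-up-only responders (w = 0.5), the error fell to 11.7% at r = 0.8 and 18.3% at r = 0.5. In the w = 0.5 runs at 10 sites, a t-test on site mean changes held 3.7% to 5.5%.

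**6. Power once the variation is carried.** At 10 sites of 100 with ICC of change 0.02, the noncentrality is 0.30 / √(4 × 2.98 / 1000) = 2.75. Against a normal reference power is 78.5%; against t with 8 df (critical value 2.306) it is 67.4%. At 14 × 50 and 19 × 30 the site-based figures are 73.6% and 76.6%.

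**The case against.** The analysis section is one condensed sentence in a journal article. It does not say intercept only, and an unseen analysis plan could add a site-by-time term. The reference to Kenward-Roger shows an intent to respect the small number of clusters. That limits the point to the model as worded. It does not remove it, because an analysis plan that follows the wording literally carries the gap forward.

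A reader might infer that the false-positive rate is well above 5% whatever the data. The document does not support that: the rate is 5% if sites do not differ in change and only modestly raised if site effects are very stable or sites are small. Cancellation is also incomplete for workers with one survey, whom the model is chosen to include, and this lowers the inflation.

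A reader might also infer that the analysis flatly contradicts the sample size. That is too strong. The ICC is reported for the intention measure, not for its change, and applying it to a difference in change may simply be cautious planning. What stands is that the sample size allows for clustering of the tested contrast and the stated model does not.

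Finally, Trial status gives 1573 workers, 74% participation and 8 sites, or about 145 respondents per site (1573 × 0.74 / 8). With a change ICC of 0.02 that would give 32%. It should not be the headline: it counts baseline respondents only, assumes all return, and treats sites of 25 to 440 workers as equal in size.

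**Conclusion.** The point holds in conditional form. On its plain reading, the stated model omits the variance component that limits a cluster trial analysed by change, and the stated degrees-of-freedom method cannot supply it. At 10 sites of 100, type I error runs from 5% (no site variation in change) through about 8% to 11% (site autocorrelation 0.9) and about 10% to 17% (0.8) to about 18% to 29% (0.5). These ranges span ICCs of 0.0112 and 0.02 and assume within-person correlation 0.5 to 0.6, equal site sizes and complete pairs. Which value applies cannot be determined from the document. The exposure falls on the only primary test, so it should be closed before analysis.

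**What to change.** State a random site intercept plus a random site-by-time effect (equivalently, site effects at both waves). Test the arm-by-time contrast with degrees of freedom based on the number of sites, about K − 2, and keep these if the site-by-time variance is estimated at zero. Otherwise the test reverts to worker-level degrees of freedom. Carry the same term into the generalised mixed models. A site-level analysis of change, weighted for unequal site size, can serve as a sensitivity check.

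This takes a sentence or two and no new data. The price is a wider confidence interval and lower power: about 67% at 10 sites of 100 if the ICC of change is 0.02, against the planned 80%. Power should therefore be rechecked with site-based degrees of freedom at the number and sizes of sites actually recruited, and restated with the assumed ICC of change made explicit.

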#### Power and sample size

We based our power and sample size calculations on the primary outcomes: intentions to seek help from formal sources. From a previous MATES trial in construction workers (“MATES Mobile,” ACTRN12619000625178) [25], we obtained clustered data with which to estimate intra-class correlation (ICC) and the corresponding design effect. Our measure of intention to seek help for emotional problems from formal sources yielded an ICC estimate of 0.0112. To be conservative, we used an ICC of 0.02. For our anticipated effect size, or Minimally Important Difference (Cohen’s d, standardised difference in change between intervention and control groups in a two-arm trial), we have used 0.30; this effect size is modest, but is in the range of what has been achieved in previous workplace suicide prevention trials. Other inputs into power calculations included: alpha = 0.05 and beta = 0.80. Because we did not know in advance what our cluster sizes would be, a set of calculations was conducted assuming a range of anticipated cluster sizes (30, 50 and 100 workers per cluster/site). At the lower cluster size of 30, we would need 19 sites, at the middle cluster size of 50 we would need 14 sites, and finally if our cluster sizes average 100 or more, we would need only 10 sites. Hence the target sample size in this protocol is estimated at 1000, based on recruiting 10 sites of 100 workers each, acknowledging that the final sample size may vary based on worksite size.

In addition, we will conduct exploratory analyses to investigate whether intervention-associated changes differ by gender or by manual blue-collar versus white-collar.

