### Trial status (as of submission)

Site recruitment commenced in December of 2021, but has been hampered by the COVID-19 pandemic and the associated restrictions and impacts on businesses. As sites were recruited, they were grouped and randomly assigned as soon as feasible, such that data collection and intervention implementation could be spread out over time and managed with the small implementation and research teams available. Two groups of four sites have been recruited and baseline data collection completed before random assignment by the procedure detailed above (running total = 5 sites assigned to intervention and 3 sites to wait-list control). Intervention activities have been initiated at most sites assigned to the intervention condition. A third and final group of sites awaits completion of baseline surveys and random assignment. The 8 sites recruited to date vary widely in size, ranging from 25 up to 440 workers, corresponding to an estimated study population of 1573 workers in total. Survey participation to date has been relatively high, with an overall average of 74% and a range of 60–92% over the 8 sites.

Though few in number, distressed workers have been identified and followed up while piloting the survey, and at both intervention and wait-list control sites during the conduct of baseline surveys; the frequency and nature of these events will be captured from Field Officer notes. While strictly speaking, this would constitute ‘contamination’ of wait-list control sites, this is a limitation that is ethically imperative and is not likely to affect the overall results of the trial.

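### The site counts allow for no variation in site size but are applied to an average: 10 sites averaging 100, spread as the recruited sites are, give typically about 72–73% power, against 78.5% with equal sizes

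*Protocol article*

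**What the plan says.** The section on power and sample size of the protocol article gives these inputs: "alpha = 0.05 and beta = 0.80" (0.80 is evidently the power), a "standardised difference in change between intervention and control groups in a two-arm trial), we have used 0.30", and for clustering "To be conservative, we used an ICC of 0.02", against an estimate of 0.0112 from an earlier trial. Sizes were not known in advance, so the calculation was run "assuming a range of anticipated cluster sizes (30, 50 and 100 workers per cluster/site"). The printed results are 19 sites for size 30 and 14 for size 50. The third result is worded differently, as a statement about a mean: "finally if our cluster sizes average 100 or more, we would need only 10 sites". The target of 1000 is 10 sites of 100. The section adds that the final sample size may differ with worksite size.

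The trial status section reports what was recruited: "The 8 sites recruited to date vary widely in size, ranging from 25 up to 440 workers, corresponding to an estimated study population of 1573". Average baseline survey participation is 74%, five sites are allocated to intervention and three to wait-list, and one further group of sites is still to come. The effectiveness analysis section says: "Cluster effects will be modelled using a random site effect".

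**The concern.** The calculation was done for sites of one fixed size, but the conclusion is worded for an average. With a positive ICC the two are not interchangeable. A site of m workers contributes information m/(1+(m−1)·ICC), which flattens as m grows: at ICC 0.02 it can never exceed 1/0.02 = 50, however large the site. Extra workers at a large site do not make up for those missing at a small one, so unequal sites always carry less information than equal sites with the same mean. The article itself shows that the sites are very unequal.

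The stake is how the result is read. If the primary comparison is null, readers will take it that the trial had 80% power for d = 0.30 because the site rule was met.

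**Working it through.** **Inputs.** From the power section: d = 0.30 (SD 1), ICC = 0.02, alpha 0.05, power 0.80. From the trial status section: 8 sites, minimum 25, maximum 440, total 1573, participation 74%. Assumed: two-sided test (this matches the printed counts), normal approximation, equal split of sites and a similar size mix in both arms.

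**1. The plan's own figures.** Total N without clustering = 4·(1.96+0.8416)²/0.30² = 348.8. Sites = 348.8·(1+(m−1)·0.02)/m.

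| m | Design effect | Sites | Printed |
|---|---|---|---|
| 30 | 1.58 | 18.4 | 19 |
| 50 | 1.98 | 13.8 | 14 |
| 100 | 2.98 | 10.4 | 10 |

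The first two are rounded up and the third down. A term for size variation would raise all three, so the printed counts leave no room for one.

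**2. Spread of the recruited sites.** Mean = 1573/8 = 196.6. The individual sizes are not given, but the four reported numbers bound the CV:
- Smallest: 25, 440 and six sites of 184.7 (CV 0.54).
- Largest: four sites of 25, three of 440 and one of 153 (CV 0.98).

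**3. Power for 10 sites averaging 100.** Rescale each set to mean 100 and average m_i/(1+(m_i−1)·0.02) over sites. Information per arm is 5 times that average, and power = Φ(0.30/√(2/information per arm) − 1.96). This is the weighting that a random-site model uses. Sites needed for 80% = 348.8/(average information per site).

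| Site sizes | Information per site | Relative to equal | Power | Sites for 80% |
|---|---|---|---|---|
| Equal | 33.56 | 1.00 | 78.5% | 10.4 |
| CV 0.54 | 31.06 | 0.926 | 75.3% | 11.2 |
| CV 0.98 | 24.37 | 0.726 | 64.9% | 14.3 |

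Random size sets that meet the reported minimum, maximum and total have median power of about 72–73% (72.3% and 72.7% in two runs). A third way of drawing the sizes gave 73.6%. One of these simulations had a 95% range of 69.7% to 74.7%.

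**4. Splitting the shortfall.** From 80% to 78.5% is rounding (1.5 points). From 78.5% to about 72–73% is unequal size (typically 5–6 points; 3.2 at the smallest possible spread).

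**5. The trial as recruited.** Mean baseline respondents per site = 1573·0.74/8 = 145.5, with the same relative spread:
- 10 sites, equal split: 70.1% to 79.8%, typically about 77% (equal sizes would give 82.7%).
- 12 sites, equal split: 77.8% to 86.5%, typically about 84%.
- The 8 sites in hand at 5:3, using Φ(0.30/√(1/(5I)+1/(3I)) − 1.96) with I = 34.75 (smallest spread) or 27.51 (largest): 67.8% or 57.7%.

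None of these allows for loss between baseline and 8 months.

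**The case against.** The strongest reply is that the recruited sites do not average 100. They average about 197 workers, or about 146 respondents. A reader might infer from step 3 that the trial being run has only 65–75% power. The documents do not support that: it takes the spread of the recruited sites and ignores their mean. At the actual mean, 10 sites fall typically about 3 points short of 80%. Twelve sites, which a full final batch of four would give, typically exceed it. This reply stands and limits the consequence. It does not rescue the rule, which is stated for a mean of 100, and the final number of sites and retention are not yet known.

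Other replies:
- **The 65% end is an extreme.** It needs four sites at exactly the minimum and three at exactly the maximum. This stands; it is a bound and not an expectation. The cruder design effect 1+((1+CV²)m−1)·ICC gives 57–71%, but it is more pessimistic than the planned random-site model and is not the right headline.
- **The ICC was set cautiously.** At 0.0112, 10 sites averaging 100 with this spread give 80.0% to 88.2%. So the shortfall depends on the plan's choice of 0.02. But 0.02 is the design value to which the 80% is attached, and the article does not offer that margin as an allowance for unequal sizes.
- **The formula is not named.** This stands; the equal-size reading is inferred. It fits 19 and 14 on rounding up, and 10 only on rounding down.
- **The article says that the final sample size may vary with worksite size.** That concerns total N, and not the efficiency lost at a given N.

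**Conclusion.** The rule is wrong as worded, by a moderate amount. With d = 0.30, ICC 0.02, two-sided 0.05, a normal approximation and a 5:5 split, 10 sites averaging 100 with the relative spread of the first 8 deliver typically about 72–73% power (bounds 65% and 75%). About 5–6 points of the gap from 80% come from unequal size and 1.5 from rounding. For the recruited trial the position is milder with 10 or 12 sites and clearly short if recruitment stops at the 8 in hand (about 58–68%).

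These figures assume that later sites resemble the first 8 in relative spread and that participation is similar across sites (the article reports 60–92%). The documents do not show that the trial as run is seriously underpowered, or that sites must be added. They do show that the printed rule cannot support a claim of 80% power.

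**What to change.** In the power and sample size section:
- Remove the rule based on average site size.
- Compute the information as the sum over sites of m_i/(1+(m_i−1)·ICC), using the known site sizes. If the sizes cannot be listed, use a design effect that includes the CV.
- Restate the power, or the detectable d, for the sites actually recruited, their expected respondents at 8 months and the actual allocation between arms.
- Name the formula, and round the site count up.

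The cost is one recalculation from sizes the trial team already holds, one rewritten paragraph and a less favourable stated power. No extra sites are required, and neither the conduct nor the analysis of the trial changes.

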## Discussion

This project represents a strong partnership bringing together practitioners at the coalface of suicide prevention (MATES), industry partners (participating sites, unions, and Steering Group), and suicide prevention researchers. Further, the trial addresses an urgent need for experimental evidence on the effectiveness of workplace suicide prevention programs, both for MATES in particular as well as for workplace suicide prevention in general [29]. The qualitative implementation evaluation aims to provide narrative insights into how the intervention gets implemented: what it “looks like” in practice [30]. The qualitative implementation evaluation will be complemented by quantitative data collection focussed on the extent to which program components were implemented as planned as well as the extent of participation in intervention activities. The combination of qualitative and quantitative methods will enable the exploration of context-specific factors that could modify intervention implementation as well as effectiveness [31].

While the cRCT design provides strong internal validity, our study may be limited with respect to external validity, or generalisability. Worksites that have engaged with the labour-management steering committee and are willing to accept the terms of an experimental study may be a select group that is not representative of all manufacturing worksites. Within sites, however, we expect that the potential for selection bias is limited, given the relatively high participation rates in the baseline surveys (average = 74%), which we will hope to retain at follow-up.

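### The site counts and the target of 1000 carry no allowance for survey non-response or loss between surveys, and do not say whether workers means site headcount or analysed respondents

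*Protocol article*

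**What the plan says.** The section on power and sample size in the protocol article uses a standardised difference in change of 0.30 and gives "alpha = 0.05 and beta = 0.80"; the 0.80 is evidently power. On clustering it says "To be conservative, we used an ICC of 0.02", against an estimate of 0.0112. For cluster sizes of 30, 50 and 100 workers per site it gives 19, 14 and 10 sites, the last for an average of 100 or more. It then concludes: "Hence the target sample size in this protocol is estimated at 1000, based on recruiting 10 sites of 100 workers each", adding that the final number may change with the size of the worksites. It mentions neither a response rate nor loss to follow-up.

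The analysis section tests change from baseline to 8 months with a mixed model for repeated measures (MMRM), chosen because it keeps participants with missing data. The trial status section reports: "Survey participation to date has been relatively high, with an overall average of 74% and a range of 60–92% over the 8 sites". On follow-up the Discussion offers only a hope: "given the relatively high participation rates in the baseline surveys (average = 74%), which we will hope to retain at follow-up".

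**The concern.** A cluster-size formula needs the number of people per site who contribute to the estimate. If the 30, 50 and 100 are people employed on site, the calculation assumes that all of them answer and are retained, while the protocol itself reports that about a quarter did not answer at baseline. Because the outcome is a change, information can be lost at both surveys.

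The wording leans towards headcount. The allocation section classifies sites as small or large by number of workers. The trial status section gives site sizes and a population of 1573 in workers, then reports participation separately. The power section ties the sample size to worksite size. At stake is whether the printed site counts and the 1000 deliver the 80% power they are meant to.

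**Working it through.** **Inputs.** From the power section: d = 0.30, alpha = 0.05, power 0.80, ICC = 0.02, cluster size m = 30, 50 or 100. Two-sided testing, equal arms and equal cluster sizes are assumed; a one-sided test would give 14.5, 10.9 and 8.2 sites and does not reproduce the printed counts. From the trial status section: participation 74% (60–92%), 8 sites, 1573 workers. The follow-up rate is not given. The range shown runs from 100% to 74% of baseline respondents.

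**Step 1: reproduce the plan's counts.** Total without clustering: 4 × (1.960 + 0.842)² / 0.30² = 348.8. Design effect: DE = 1 + (m − 1) × 0.02. Sites = 348.8 × DE / m.

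- m = 30: DE 1.58, 18.4 sites (printed 19)
- m = 50: DE 1.98, 13.8 sites (printed 14)
- m = 100: DE 2.98, 10.4 sites (printed 10)

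The counts reproduce without any loss term. The first two are rounded up and the third is rounded down.

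**Step 2: power at the printed counts.** With k sites, power = Φ(0.30 × √(k × m / DE / 4) − 1.96). For 10 × 100 analysed, the effective total is 1000 / 2.98 = 335.6, and power is Φ(2.748 − 1.960) = 78.5%. Eleven sites give 82.2%.

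**Step 3: treat the printed size as headcount.** Analysed workers per site are 0.74 × m with no further loss, or 0.74 × 0.74 × m = 0.5476 × m if retention is also 74% and only complete pairs count.

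| Design | All analysed | 74% respond, none lost | 74% respond, 74% of those retained |
|---|---|---|---|
| 10 × 100 | 78.5% | 73.9% (74 per site, DE 2.46) | 68.3% (54.8 per site, DE 2.08) |
| 14 × 50 | 80.5% | 74.0% | 66.1% |
| 19 × 30 | 81.3% | 73.3% | 63.9% |

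At a headcount of 100, 80% power would need 11.6 (12) or 13.2 (14) sites. Of the shortfall at 10 × 100, 1.5 points come from rounding, 4.5 from baseline non-response and a further 5.6 from the assumed follow-up loss.

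**Step 4: sensitivity.** For 10 × 100 with no follow-up loss, participation of 60% gives 70.1% power and 92% gives 77.3%. At the estimated ICC of 0.0112, power is 85.7% with 74 analysed per site and 79.2% with 54.8.

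**Step 5: the sites recruited.** Mean headcount is 1573 / 8 = 197. At 74% that is 146 baseline respondents per site, and at 74% again, 108 with both surveys. Ten equal sites of that size would give 82.7% and 79.4% power.

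**The case against.** The strongest reply is that the article never says the 100 are headcount. It calls the 1000 a sample size and uses a different term, study population, for the 1573. If the 1000 are respondents, baseline non-response is already outside the calculation and only follow-up loss remains. This stands: a reader might infer that the plan knowingly counts every on-site worker as analysed, but the text only favours the headcount reading. It does not rescue the 10 × 100 figure, which gives 78.5% with everyone analysed.

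Second, the 68% rests on a retention rate that appears nowhere in the document and on complete pairs only. MMRM also uses workers with one survey. This stands too: they add a little to an estimate of change, so 68% is a lower figure under that assumption. MMRM recovers nothing from workers who answer neither survey. The 74% power figure needs no follow-up loss at all.

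Third, the ICC was raised from 0.0112 as a margin. That margin would offset much of the loss, but it was taken for uncertainty in the ICC, and 0.02 is the planning value behind the printed counts.

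Fourth, the recruited sites are larger than planned. A reader might infer that the trial itself has 68–74% power, or that a team counting headcount would stop recruiting too early. The document supports neither. Headcount had reached 1573 with a third group of sites still to be randomised, and 1573 × 0.74 is about 1164 baseline respondents. The figures for larger sites do assume ten equal sites, whereas actual sizes run from 25 to 440.

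**Conclusion.** The point holds as a gap in the written sample-size statement. The counts of 19, 14 and 10 contain no allowance for non-response or loss, and the unit of cluster size is undefined. At 10 × 100, the stated 80% is missed on either reading: 78.5% if all 100 are analysed; if 100 is headcount, about 74% at the reported participation and about 68% as a lower figure with 74% retention. On the headcount reading the 50- and 30-worker scenarios also fall short; on the respondent reading both reach 80% before any follow-up loss.

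These results rest on a two-sided test, a normal approximation, equal sites and arms, and an ICC of 0.02. They describe the written target. For the trial as recruited, the shortfall from non-response is smaller because the sites average 197 workers. Apart from the rounding at 100 per site, the printed arithmetic is sound for its inputs; the fault is an unstated allowance and an undefined unit.

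**What to change.** In the power section, define cluster size and the target of 1000 as workers analysed for the change contrast. State the 74% baseline participation and an explicit retention assumption, shown as a range because no follow-up rate is yet available. Then either restate the power at 10 × 100 or correct the site counts (11 at 100 analysed; 12 or 14 at a headcount of 100 under the two retention assumptions above), and report power for the recruited site sizes alongside.

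The cost is a recalculation from data already held and a few sentences of text. No extra recruitment is needed if the power is restated. The downside is a less favourable stated power for the written target.
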